## Abstract

**Background:**

After the first six months of exclusive breastfeeding, children are introduced to liquids and semi-solid food, known as the complementary feeding phase. This phase is critical because it is often accompanied by improper feeding in children, which may lead to wasting and other nutrition problems. Fortified biscuits have been provided for wasting children as a nationwide programme. However, the ability of children to accept food supplementation remains questionable. This paper describes the protocol of a study investigating the efficacy of food supplementation (PMT biscuit) and nutrition education to improve the nutritional status of wasting children in Indonesia.

**Method:**

The efficacy of a government food supplementation programme will be examined using a randomized control trial design. Parents with wasting children aged 6–17 months will be recruited to participate in the study. After obtaining informed consent and pre-intervention measures, participants will be assigned into three arms of intervention with PMT biscuits and/or nutrition education only. The two primary outcomes for this study are the nutritional status of wasting children and PMT biscuit compliance. Characteristics of all subjects in each arm will be analysed and compared with each other to assess their comparability at the beginning. The data will be collected at pre-intervention, at 3 months of intervention, post-intervention, and at the 6- to 9-month follow up.

**Discussion:**

This paper aims to describe the study protocol of a randomized controlled trial investigating the effects of different PMT biscuit portion and nutrition education in two arms and nutrition education only in another arm. This study is important because it will provide evidence for the Indonesian government regarding the efficacy of food supplementation and/or food-based recommendations to improve the nutritional status of wasting children aged 6–23 months in Indonesia.

**Trial registration:**

The study has been registered at clinicaltrials.gov, maintained by the National Library of Medicine (NLM) at the National Institutes of Health (NIH), on April 26, 2018, and was last updated on April 30, 2018 (registration number: NCT03509155).

## Background

Children under 5 years of age undergo a period of rapid growth and development. Therefore, this age group needs attention because of their vulnerability to malnutrition. In Indonesia, children under 5 years of age with undernutrition (weight-per-age) and wasting (weight-per-height) remain greater than 10%. Feeding practices in compliance with the WHO standard is a concern that needs to be addressed using a community health programme approach [1, 2].

According to the concept of the first 1000 days of life, the possibility of improvement opportunities for a child that develops undernutrition or wasting problems can only be exploited within the first 2 years. Thus, the chances of the child achieving optimal growth within the next age range will be greater [3]. Food supplementation is comprehensively provided by the Indonesian government to pregnant mothers, children under 5 years of age, and school children to improve their nutritional status to achieve their best physical and intelligent development.

In the first program, food supplementation activity was provided in the form of a cash transfer to identified vulnerable families to enable them to have a suitable food supplement for their families. In 2001, the cash transfer programme was then modified to food supplementation of factory-made biscuits using a special formulation that was fortified with vitamins and minerals. This food supplementation was designed for children aged 6–59 months whose nutritional status fell into the wasting category (weight-for-height less than − 2 SD). The food supplementation was suggested to be given alongside breast milk and their daily food. The biscuit provided to children under 5 years of age was designed to add nutritional needs required to reach the age-appropriate weight. Food supplementation for children under 5 years of age was given to the children who were not indicated for hospitalization.

After the first 6 months of exclusive breastfeeding, children are introduced to liquid and semi-solid food. Children aged above 1 year are introduced to solid food or a family diet [4]. With most undernutrition children coming from low-socioeconomic families, a concern was raised whether this food supplementation will create another form of dependency as in the Indian study of the Ready to Use Therapeutic Food (RUTF) programme [5]. Thus, the sustainability of families and mothers to provide good nutritious food for children during and after the time of food supplementation needs to be assessed.

Another aspect to be explored is assessing whether the efficacy of food supplementation to improve the nutritional status of wasting children in multiple cities to describe Indonesian geographical and socio-economic diversity is necessary. This randomized controlled trial is aimed to assess the efficacy of food supplementation provided by the government and/or food-based recommendations in improving the nutritional status of wasting children aged 6–23 months in Indonesia.

### Characteristics of the fortified biscuits as a food supplement

The characteristics of the fortified biscuits are based on their texture, taste, colour, weight, safety, and expiration date. The biscuits have a crunchy texture that softens immediately when mixed with a liquid (water or milk), and they have a sweet taste and a normal cook-processed (not burnt) colour. The biscuits are prepared to meet the quality and safety requirements for infants and young children. All the products expire 24 months after production. The product should be eligible for consumption at the time between the production date and expiration date. The biscuit box uses three-layered packaging to ease the storage and provision of separate portions, as shown in Fig. 1.

**Fig. 1 Fig1:**
[figure not shown]
Packaging content and form

The primary package contains four biscuits with weights no less than 40 g containing 160 cal, 3.2–4.8 g of protein, and 4–7.2 g of fat. The food supplementation biscuits are enriched with ten vitamins (A, D, E, K, B1, B2, B3, B6, B12, and folic acid) and seven minerals (iron, iodine, zinc, calcium, sodium, selenium, and phosphorus). One secondary box contains twenty-one primary packages weighing 840 g. One tertiary packaging contains 4 secondary packages.

Technical instructions for biscuit provisions as food supplementation are clearly mentioned in the tertiary package and include the targeted children, dose, and serving. Supplemental food in the form of biscuits is indicated for children aged 6–59 months who are wasting (weight-for-height less than − 2 SD). Children aged 6–11 months and 12–59 months are suggested to consume eight biscuits (2 packages) per day and 12 biscuits (3 packages) per day, respectively. The children underwent monthly weight gain monitoring in the village-based integrated growth monitoring post *(pos pelayanan terpadu = posyandu).*

Food supplementation is stopped if the child has reached the appropriate weight and is suggested to continue with balanced nutrition family food. Biscuits could be either directly consumed or in the form of mushy food by adding more water onto the biscuits in a clean bowl. To maintain their well-nourished condition, children are recommended to have balanced nutrition appropriate for their age.

## Methods/design

This study is an open-label randomized controlled trial with three parallel arms for the intervention of food supplementation (PMT biscuit) management. The design of this study was developed using SPIRIT guidelines by Chan A-W et al. [6]. The first arm was performed as a control group obtaining only routine IYCF counselling by the health cadres and without the provision of biscuits, while the second arm was similar to the first intervention group but received fortified biscuits with a portion as recommended by the Ministry of Health and was given IYCF counselling by the cadres and nutritionist. The third arm was similar to the second intervention group but received biscuits with an adjustment in portions and IYCF counselling that emphasized the optimization of local food. IYCF counselling promoted complementary feeding recommendation (CFR) that was optimized using a linear programming approach. Adjustment in the biscuit portions in the third arm is calculated based on the nutrient gap between the nutrient requirements and optimized CFR.

In the 2nd and 3rd arms, the intervention is administered for 3 months according to the recommended duration of biscuit delivery by the Ministry of Health. Monitoring is conducted every month during treatment and will be followed in the sixth and ninth months from the beginning of the intervention.

### Study subjects

This study uses the following inclusion criteria: children aged 6–17 months with a weight-for-length z score less than 2.00 to − 2.99 considering that the children are still categorized as children under 2 years of age at the end of the intervention. The other criterion is that they do not receive the biscuits at the time of recruitment and the subjects’ parents agree to participate in the research by signing the informed consent document.

During the determination of study eligibility, four populations were identified that are inappropriate for entry into the food supplementation (biscuit) randomized controlled trial, including the severe wasting (weight-for-length less than − 3 Z-score) population because it needs to be treated differently and because it is strongly associated with a very high short-term mortality risk [7].

The exclusion criterion of this study is a severe food insecurity status of the households because their access to nutritional food is severely hampered, affecting not only the young children but also all family members.

Despite poor dietary intake, infection is also considered a determinant of nutritional status; therefore, having tuberculosis infection (based on anamnesis) is also used to exclude the subjects. Having TB infection as a co-infection in parallel with acute malnutrition was found to be a predictor of child mortality [8].

To minimize the loss to follow-up subjects, the possibility of moving to other cities within 6 months of intervention is also listed as an exclusion criterion. All the terms and conditions of the study will be explained before the caregiver/parents sign the inform consent documents.

Adverse events will be recorded and immediately reported to the PIC through the centres’ coordinators, and those affected will be referred to the nearest public health centres involved in the study. All severe adverse events will be reported to the Health Research Ethics Committee of FKUI/RSCM.

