### Outcome measures

Primary: Nutritional status of wasting children.

The measurement will be recorded through study completion, from baseline and at third, sixth, and ninth months. Anthropometry measurements will be based on the weight-for-length indicator (WHO Child Growth Standards).Secondary: PMT biscuit compliance.

The measurement will be recorded through study completion, at the first to third months after the start of treatment and then at the sixth and ninth months from the beginning of treatment.

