### Plan of data analysis and presentation

All data analysis will be performed using SPSS version 20. The data of the study subjects, both children characteristics and mother/caregiver characteristics, will be analysed to obtain the distribution frequencies and central tendencies as appropriate to the data scale. All subject characteristics of each arm will be analysed and compared with each other to assess their comparability at the beginning. No missing data are expected, and all loss to follow-up study participants will be excluded. The comparison of the weight-per-length score between groups and between times will be performed using ANOVA. The study subjects’ compliance to take biscuits will also be analysed and reported. The final dataset will be accessible to all authors without masking.

The research team is responsible to make annual and final reports to the Ministry of Health. The dissemination of the study results will be presented at the national nutritional meetings in the three regions. The scientific publications are the rights and responsibility of the research team.

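### On its plain reading the relocation exclusion stops at month 6, short of the month-9 primary-outcome visit, and the analysis then drops children who are lost

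*Protocol article*

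**What the plan says.** All references are to the protocol article.

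- **Study subjects.** The purpose of the criterion is given as "To minimize the loss to follow-up subjects", and the criterion itself is that "the possibility of moving to other cities within 6 months of intervention is also listed as an exclusion criterion". The text does not say whether the 6 months run from the start or the end of the intervention.
- **Methods/design.** In arms 2 and 3 "the intervention is administered for 3 months according to the recommended duration of biscuit delivery by the Ministry of Health". Children "will be followed in the sixth and ninth months from the beginning of the intervention".
- **Outcome measures.** The primary outcome is nutritional status by weight-for-length, recorded "from baseline and at third, sixth, and ninth months".
- **Plan of data analysis and presentation.** "No missing data are expected, and all loss to follow-up study participants will be excluded". Weight-for-length is compared between groups and between times by ANOVA.
- **Sample size.** The calculation uses a difference of 0.30 Z-score, SD 0.95, 95% confidence, 80% power and 20% drop-out, and states 540 subjects. The 20% is not tied to any visit.
- **Place and time of execution.** Seven sites are listed, enrolment was completed in April 2018, and final data collection was expected in December 2018.

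**The concern.** A criterion whose declared purpose is to reduce loss to follow-up should reach the last visit at which the primary outcome is measured. This one, read plainly, reaches month 6, while the primary outcome runs to month 9. A family that says at screening that it will leave in month 7 or 8 passes the criterion and will probably have no month-9 measurement.

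The analysis rule adds to the cost. It excludes lost participants, not missing visits. Applied literally to a comparison across times, it removes the whole child, including the month-3 value at the end of the biscuit period and the month-6 value, both already collected. Precision is lost at visits where nothing is missing. The comparison is also confined to children who stayed, in an open-label trial where families know their arm.

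**Working it through.** **Timeline, in months from the start of intervention**

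| Element | Reaches month |
|---|---|
| Biscuit intervention | 3 |
| Relocation exclusion, counted from the start | 6 |
| Relocation exclusion, counted from the end of intervention | 3 + 6 = 9 |
| Last primary-outcome visit | 9 |

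Methods/design counts the later visits from the beginning of the intervention, so counting the exclusion the same way is the plain reading. It leaves 9 − 6 = 3 months uncovered. Counting from the end of the intervention would close the gap, but the document does not say that this is meant.

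**The plan's own sample size.** The two-means formula with two-sided alpha 0.05 and 80% power gives

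n per arm = 2 × (1.960 + 0.842)² × 0.95² / 0.30² = 157.4, rounded up to 158.

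- Dividing by 1 − 0.20 gives 198 per arm, 594 in total.
- Multiplying by 1.20 gives 190 per arm, 570 in total.
- With no drop-out the total is 474.
- One-sided versions give 465, 447 and 372 respectively.

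None of these equals 540, which fits the stated inputs only with drop-out of about 12% (1 − 158/180 = 0.122). That is a separate matter. It matters here only because it is why power at 180 per arm with 20% loss starts below 80%.

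**Sensitivity of power to loss.** Inputs are a difference of 0.30, SD 0.95 and two-sided alpha 0.05, using the noncentral t distribution with lost children dropped. The arm sizes are 540/3 = 180 (the stated minimum) and 7 × 90/3 = 210 (if all seven listed sites recruit 90 each).

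| Loss | Evaluable of 180 | Power | Evaluable of 210 | Power |
|---|---|---|---|---|
| 20% | 144 | 76.1% | 168 | 82.3% |
| 25% | 135 | 73.4% | 157.5 | 79.8% |
| 30% | 126 | 70.4% | 147 | 77.0% |

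The 25% and 30% rows are assumptions; the document gives no migration rate. They represent 5 or 10 further percentage points lost between months 6 and 9. As another assumption, if the 20% applied to month 6 and loss continued at a constant rate, loss by month 9 would be 1 − 0.80^(9/6) = 28.4%, within the range shown. If the 20% already runs to month 9, only the first row applies and the criterion adds nothing to the planned loss. All figures ignore clustering.

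**The case against.** Several points on the other side have force.

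1. **The window may already reach month 9.** Six months counted after a three-month intervention ends at the last visit. The wording permits this, so a reader who infers a certain three-month gap goes further than the text. What stands is that the origin is unstated, that the rest of the design counts from the beginning, and that seven sites could apply the wording differently.
2. **The numbers may be small or already allowed for.** Only families who foresee a move at screening, and only in the last three months, are affected. A reader might infer that power falls to 70–73%. The document does not support that: the extra loss is assumed, the 20% has no time point, and 210 per arm gives 77–80% under the same assumed losses.
3. **Bias is possible, not shown.** Nothing in the document says that late moves relate to arm or to weight-for-length. The open-label design leaves room for it and no more.
4. **A criterion meant to minimise loss need not eliminate it.** This is fair, and the drop-out allowance exists for the remainder. But the allowance protects numbers only. It does not recover the month-3 and month-6 data, and it sits badly beside the expectation of no missing data.
5. **Enrolment has closed.** Changing the criterion now affects no enrolled child. This stands in full, and it moves the remedy to the analysis.

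It can also be said that the exclusion rule might be applied visit by visit, so that a child lost at month 9 still counts at month 3. The text speaks of participants, not visits, and should say so if that is the intention.

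**Conclusion.** The mismatch is real on the plain reading: the exclusion reaches month 6, the primary outcome reaches month 9, and children lost in between are removed from the analysis, literally with their earlier valid values.

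Its size cannot be derived from the document. Under the assumed extra losses, the part attributable to late moves is about 3 to 6 percentage points of power: 76.1% to 73.4% or 70.4% at 180 per arm, and 82.3% to 79.8% or 77.0% at 210. It is zero if the 20% already covers loss to month 9 or if the window was meant to run from the end of the intervention.

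The conclusion rests on counting the window from the start of intervention and on reading the exclusion rule literally. The analysis rule is the more consequential half, and the only one that can still help the enrolled children.

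**What to change.** **Analysis.** Replace the rule that excludes everyone lost to follow-up, together with the ANOVA, by a mixed model for repeated measures of weight-for-length Z-score. It should use every observed visit of all allocated children, with arm, visit and their interaction. A child who leaves after month 6 then still contributes the earlier values. Remove the statement that no missing data are expected, since the sample size plans for 20% drop-out. Report month-9 losses and their reasons by arm.

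**Criterion.** State the time origin of the 6-month window as it was applied at the sites. For any further recruitment, align it with the month-9 visit.

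**Cost.** Slightly more analysis work and some changes of wording; the planned sample size does not change. Any further recruitment would see a few more exclusions at screening. The mixed model relies on losses being explained by the observed data, which the report of losses and reasons by arm helps the reader to judge.

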### Data to be collected

The following data are collected based on the study subjects: subject characteristics (age, sex, and history of disease) and anthropometry (body weight and body height) data. Other data collected from the subjects’ mother/caregiver include the subject characteristics (demographic, socioeconomic, house condition), food intake of the child [using 24-h food recall for 3 days and last 1 week food frequency questionnaire (FFQ)], and perceptions of the supplemental biscuits (packaging and delivery method). The same method is also used to collect data for compliance with feeding instructions, exposure to information (health information sources, health information ever obtained in Posyandu/health services post), and IYCF-related knowledge. The flowchart for data collection is shown in Fig. 2.

**Fig. 2 Fig2:**
[figure not shown]
Flowchart of the data collection

### Sample size

The sample size is calculated using the two means comparison formula. Based on Afarwuah, the standard deviation is obtained at 0.95 [9]. The sample size calculation is performed using the 95% confidence level, 80% power, and an estimated difference in the weight-for-length Z-score and drop-out of 0.30 and 20%, respectively. Based on the formula and data used above for the minimal sample size, 540 subjects are required for this study. Considering the feasibility of subject and study implementation, 90 subjects per district are required: 30 subjects as a control group or arm 1, and 30 subjects each as intervention group 1 or 2 (arm 2 or 3). Thus, a minimum of 6 districts is needed to meet the minimum sample size required.

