### Sampling method

The sampling procedure is started by selecting provinces and districts in cooperation with the Ministry of Health. Next, among sub-districts with a moderate prevalence of wasting children, three are selected to become arms of the study. The prevalence rate of moderate wasting is 10–15%, and the decision to include moderate wasting is to maintain the heterogeneity conditions of the selected sub-districts. Three selected sub-districts are then selected randomly to be assigned as arm 1 (control) and arms 2 and 3 (intervention 1 and 2, respectively). Subjects are generated from *posyandu*, from which only those with 2–5 eligible children were chosen. Thus, to fulfil the total number of 30 subjects, each sub-district involves 6–15 *posyandu*. Expansion to another sub-district will be done when there are fewer than 30 wasting children aged 6–17 months in each selected sub-district. The sampling method scheme is provided in Fig. 3.

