### Place and time of execution

Data collection will be conducted in 7 selected sites in Indonesia in accordance with Ministry of Health Coordination (Sambas Regency - West Borneo [1.3625° N, 109.2832° E], Depok Municipality – West Java [6°24′8.94″S, 106°47′39.27″E], Padang Pariaman Regency – West Sumatra[0.5547° S, 100.2152° E], Sleman Regency – Yogyakarta [7.7325° S, 110.4024° E], Banjar Baru Municipality – South Borneo [3°27′26.07″S, 114°48′37.14″E], Sidoarjo Regency – East Java [7.4726° S, 112.6675° E], Makassar Municipality – South Sulawesi [5°8′39.76″S, 119°25′35.9″E]). Data from each site are collected by investigators from 7 research centres of respected universities in Indonesia (SEAMEO RECFON, Faculty of Public Health Universitas Indonesia; Faculty of Public Health Andalas University; Faculty of Public Health Lambung Mangkurat University; Faculty of Medicine, Public Health, and Nursing Universitas Gadjah Mada; Faculty of Public Health Airlangga University; Faculty of Public Health Hasanuddin University). SEAMEO RECFON serves as a lead investigator. This study is planned for 3 months using a grant scheme in 2017 so that implementation in the 6th and 9th months will be continued in 2018. The enrolment of the study participants was initiated in January 2018 and finalized in April 2018. It is expected that the final data collection would be in December 2018.

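### The 540 subjects and 6 districts do not follow from the protocol's own inputs, and the calculation ignores allocation by sub-district, so the stated 80% power is not supported

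*Protocol article*

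**What the plan says.** The Sample size section of the protocol article sets out a full derivation. On the method it says "The sample size is calculated using the two means comparison formula". The planning SD is taken from a cited study: "the standard deviation is obtained at 0.95". The error rates follow: "The sample size calculation is performed using the 95% confidence level, 80% power". The difference is 0.30 in weight-for-length Z-score and the drop-out 20%. The result is "Based on the formula and data used above for the minimal sample size, 540 subjects are required for this study". At 90 children per district, 30 in each arm, the section concludes: "Thus, a minimum of 6 districts is needed to meet the minimum sample size required". It mentions no design effect and no ICC.

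Three other sections bear on this:

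- **Sampling method** gives the unit of allocation: "Three selected sub-districts are then selected randomly to be assigned as arm 1 (control) and arms 2 and 3". Each sub-district is to supply about 30 children, all in the same arm.
- **Plan of data analysis and presentation** compares weight-for-length by ANOVA, mentions no cluster term, and excludes children lost to follow-up.
- **Place and time of execution** states: "Data collection will be conducted in 7 selected sites in Indonesia". This is one site more than the stated minimum, and the protocol does not link it to the sample-size requirement.

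**The concern.** There are two separate faults. The total of 540 is presented as the output of a named formula with stated inputs, and that formula does not return it. The formula also treats children as independently randomised, whereas the Sampling method section randomises whole sub-districts. Children in one sub-district share health staff, counselling, food supply and infection exposure, so their outcomes are likely to be correlated, and the comparison between arms rests on 6 or 7 sub-districts per arm.

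Weight-for-length is the primary outcome, and the trial is meant to inform government policy on the biscuit programme. A null result, for biscuits against control or for the reduced against the standard portion, would be read as coming from a trial with 80% power when the real figure may be well below that.

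**Working it through.** **Inputs.** From Sample size: SD 0.95, difference 0.30, alpha 0.05, power 80%, drop-out 20%, 30 children per arm per district. Sidedness is not stated, so both were tried. The ICC is an assumption, because the protocol gives none.

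**Step 1. Attempt to reproduce 540.**

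n per arm = 2(z₁₋α/₂ + z₁₋β)² SD²/δ² = 2(1.960 + 0.8416)² × 0.95²/0.30² = 157.4, so 158 evaluable.

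| Version | Evaluable per arm | Enrolled per arm | Total, 3 arms |
|---|---|---|---|
| Two-sided, n/(1 − 0.2) | 158 | 198 | 594 |
| Two-sided, n × 1.2 | 158 | 190 | 570 |
| One-sided, n/(1 − 0.2) | 124 | 155 | 465 |
| One-sided, n × 1.2 | 124 | 149 | 447 |

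None gives 540. A Bonferroni correction moves further away (239 enrolled per arm for two comparisons, 263 for three).

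**Step 2. Districts.** 594/90 = 6.6, so at least 7, not 6.

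**Step 3. Power for independent children.**

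- 540 enrolled: 180 × 0.8 = 144 evaluable per arm, power 76%. The 180 per arm would suffice only with drop-out of about 12% (1 − 158/180 = 0.122).
- 7 sites of 90: 630 enrolled, 210 × 0.8 = 168 evaluable per arm, power 82%.

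**Step 4. Power with sub-districts as the unit.** Take one sub-district per arm in each of k districts, 30 × 0.8 = 24 evaluable children in each, with district as block:

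SE = √[2 × 0.95² × (ICC + (1 − ICC)/24)/k]

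This is the Step 3 variance multiplied by the design effect 1 + 23 × ICC. With three arms in k blocks the t reference has 2(k − 1) degrees of freedom. For example, k = 7 and ICC = 0.02 give SE = √[1.805 × (0.02 + 0.98/24)/7] = 0.125, and 0.30/0.125 = 2.40 on 12 df gives 60% power.

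| Assumed ICC | Design effect | 6 districts, t (10 df) | 6 districts, normal | 7 districts, t (12 df) | 7 districts, normal |
|---|---|---|---|---|---|
| 0.005 | 1.115 | 63% | 72% | 71% | 78% |
| 0.01 | 1.23 | 59% | 68% | 67% | 74% |
| 0.02 | 1.46 | 52% | 60% | 60% | 67% |
| 0.05 | 2.15 | 38% | 45% | 44% | 51% |

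Even by the normal approximation, 7 sites fall below 80% once the ICC exceeds about 0.003.

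**Step 5. Detectable difference.** At 7 districts and ICC 0.01 to 0.05, the difference detectable with 80% power is 0.35 to 0.46 Z (t reference) or 0.32 to 0.43 Z (normal), against the planned 0.30.

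**The case against.** The strongest reply is that the arithmetic slip does no harm to the trial as planned. The 540 and the 6 districts are stated as minimums. Seven sites are listed, and 630 exceeds 594. This is correct if each site enrols 90, and it makes the arithmetic error the lesser of the two. It does not make the stated figures right, and it leaves the clustering untouched.

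The size of the clustering loss is also open to challenge, on four grounds:

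- **The ICC is assumed.** Power at 7 sites falls below 50% only at the top of the range and only with the t reference. The direction of the loss is sure; its size is not.
- **The t reference contributes.** At ICC zero and 7 districts it gives 76%, against 82% for independent children. That cost comes with having few units of allocation, but both sets of figures belong in view, and the normal approximation also falls short of 80% at every ICC shown.
- **The SD may be smaller**, because entry is confined to about one Z unit. With an assumed SD of 0.80, the t-based power at 7 districts is 81%, 74% and 58% at ICC 0.01, 0.02 and 0.05. This could recover much of the loss. But 0.95 is the protocol's own planning value, and the 80% claim has to be judged on it.
- **The number of sub-districts may grow.** The Sampling method section allows expansion to another sub-district where fewer than 30 eligible children are found, so exactly 7 units of 24 completers per arm is a simplification.

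Finally, a three-group F-test with means 0, 0.3 and 0.3 needs 525 or 547 subjects, depending on how drop-out is added, which is close to 540. The protocol names a two-means formula, however, and an overall F-test does not power the pairwise comparisons.

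**Conclusion.** The concern holds. On the stated inputs the requirement is 594 subjects and 7 districts, not 540 and 6. Taken alone this is a modest error: 76% power instead of 80%, and covered by 7 sites of 90. The missing allowance for sub-district allocation matters more and remains at 7 sites. For assumed ICCs of 0.01 to 0.05, power there is 67% to 44% with a t reference, or 74% to 51% with a normal approximation. These figures rest on SD 0.95, 24 completers in each sub-district, one sub-district per arm in each district, and an ICC the protocol does not supply. The stated 80% is therefore unsupported on the protocol's own SD, and the paragraph must be corrected.

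**What to change.** Rewrite the Sample size paragraph as follows:

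1. Replace 540 with 594 (198 per arm) and 6 districts with at least 7, labelled as the requirement before clustering. State that the test is two-sided.
2. Cite the 630 children planned at 7 sites and say that this assumes 90 per site.
3. Add the design effect 1 + (m − 1) × ICC, with m the evaluable children per sub-district and a justified range of ICCs.
4. Restate the power, or the difference detectable with 80% power, that 7 sub-districts per arm give. If a smaller SD is thought realistic for this entry band, justify it and show it beside 0.95.

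The cost is one reworded paragraph and a less favourable power statement. No extra enrolment is asked for.
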